## Abstract

**Background:**

The survivors after hip fracture often report severe pain and loss of physical functioning. The poor outcomes cause negative impact on the person’s physical functioning and quality of life and put a financial burden on society. Rehabilitation is important to improve physical functioning after hip fracture. To maintain the continuity in rehabilitation we have an assumption that it is of utmost importance to continue and progress the functional training that already started at the hospital, while the patients are transferred to short-term stays in a nursing home before they are returning to home. The aim presently is to examine the effects of a functional training program, initiated by the physiotherapist and performed by the nurses, on physical functioning while the patients are at short term stays in primary health care.

**Methods/design:**

Inclusion and randomization will take place during hospital stay. All patients 65 years or above who have sustained a hip fracture are eligible, except if they have a score on Mini Mental State (MMS-E) of less than 15, could walk less than 10 m prior to the fracture, or are terminally ill. The intervention consists of additional functional training as part of the habitual daily routine during short term stays at nursing homes after discharge from hospital. The primary outcome is physical functioning measured by the Short Physical Performance Battery (SPPB). Secondary outcomes are Timed “Up & Go” (TUG), hand grip strength, activPAL accelerometer, and self-reported measures like new Mobility Score (NMS), Walking Habits, University of California Los Angeles (UCLA) activity scale, Fall efficacy scale (FES), EuroQol health status measure (EQ-5D-5 L), and pain.

**Discussion:**

Issues related to internal and external validity in the study are discussed. The outline for the arguments in this protocol is organized according to the guidelines of the Medical Research Council (MRC) guidance on how to develop and evaluate complex interventions.

**Trial registration:**

ClinicalTrials.gov NCT02780076.

## Background

Hip fracture (a fracture of the upper part of the femur), is a worldwide health problem in old age [1, 2]. World-wide, there are approximately 1.7 million hip fractures each year. The highest rates are seen in North America and Europe [1]. In Norway (with 4.7 million inhabitants), about 9000 patients are hospitalized and operated for hip fractures annually. This is among the highest reported hip fracture incidence rates in the world [1–3], even though the hip fracture rates in Norway have declined during the past 15 years. Nevertheless, the forecasted growing number of older people might cause an increase in the absolute number of fractures. This may lead to a substantial, societal, economic and public health burden [4]. Hip fracture is a serious event; one out of every four patients die within one year. Survivors often report severe pain and loss of physical functioning [3].

In a systematic review it was estimated that 42% of survivors after hip fracture did not return to their pre-fracture level of physical functioning, and 35% became incapable of walking independently after the fracture [5]. Moreover, 50% of those able to walk without a walking device before the fracture became permanently dependent on a walking device, and 50% of survivors had persistent loss of independence in daily activities after the fracture [6, 7]. Long-lasting mobility limitations after hip fracture may lead to prolonged physical disability, increased fall risk and new injuries, and 15% of the patients will become permanently institutionalized [7]. Altogether, these impairments cause considerable suffering. Therefore, strategies for hip fracture rehabilitation to enhance the patients’ recovery of physical functioning and prevent future falls is an urgent health care challenge. With such serious consequences, prevention and treatment of fractures to improve outcomes are crucial.

In Norway, the mean length of hospital stay (LOS) after hip fracture surgery is 5–6 days [8]. An increasingly shorter LOS is in line with international studies showing that aging patients are discharged from the hospital “quicker and sicker” [9, 10]. After discharge, most of the patients in Norway are transferred to short-term stays in nursing homes in primary health care before they are able to return to home.

Functional training, such as walking and transfers, ought to be an important part of the rehabilitation after hip fracture. Nevertheless, research indicates that rehabilitation strategies after hip fracture vary [11–13]. Experts agree that for better survival rate and for improvement of pain, quality of life and physical functioning, early assisted ambulation should begin while the patients are in hospital [10–12]. According to a systematic review and two Cochrane reviews [14–16], there are no set guidelines for best practice training programs after discharge from hospital. To maintain the continuity in rehabilitation, we have an assumption that it is of utmost importance to continue and progress the functional training during the sub-acute phase while the patients are at short-term stays in nursing homes. However, in the nursing homes the resources of physiotherapists and nursing staff seem to be limited, and the nursing staff involved may only to a small extent be focused upon enhancement of the patients’ physical functioning. These assumptions are supported by a study that examined the nurses’ experiences and attitudes towards rehabilitation after hip fractures [17]. The nurses working in the nursing homes, as opposed to the nurses at the hospital, seemed to be less concerned with their role and participation in the patients’ rehabilitation process [17]. Therefore, the possible discontinuity in the rehabilitation efforts during short-term stays may have a negative impact on the patients’ recovery of physical functioning.

Progressive resistance training is found effective in improving physical functioning in the frail elderly [18] and in patients after hip fracture surgery [13, 19]. However, progressive resistance training may be difficult to carry out in the sub-acute phase, partly because of limited recourses, and partly because of the patients’ pain and health condition after surgery. An option may therefore be to continue and progress the functional training started during hospital stay, such as training in walking and further on repetitive sit-to-stands, as part of the daily habitual routine during their short-term stays in the nursing homes [20]. This type of functional training may be motivational and easily recognizable to the patients, and it can also be carried out by the nursing staff with only initial guiding from a physiotherapist. There seems to be lack of knowledge on the effect of additional functional training, incorporated as part of the habitual daily routine during short-term stays, on the patients’ immediate and long term recovery of physical functioning and activity level after hip fracture, compared to usual care alone.

### Aims

#### Primary aim

To assess the immediate and long-term effects of an additional functional training program, performed in a population of frail older patients with low energy hip fracture, as part of the habitual daily routine during their short-term stays in nursing homes, on physical functioning measured by the Short Physical Performance Battery (SPPB).

#### Secondary aims

To assess the immediate and long-term effects of the same program on ambulation, level of physical activity, health-related quality of life, pain in rest and while walking, fear of falling, number of secondary falls, support from health care services, place of residence, mortality rate, and the cost-effectiveness of the intervention.

## Methods/Design

### Project context

The present study is undertaken at Bærum Hospital Vestre Viken and in Bærum municipality, located nearby Oslo, Norway. Bærum Hospital serves as a local hospital for about 300 000 inhabitants, and approximately 350 patients are treated surgically for hip fractures at the hospital each year. The patients are hospitalized in the orthogeriatric section within the Department of Orthopedic Surgery. An orthogeriatric approach involves several medical- and healthcare disciplines, such as geriatrician, orthopedic surgeon, nurse, physiotherapist, occupational therapist, and pharmacist [21–23]. The team examines the patients and evaluates their medical-, functional-, and cognitive status, risk of secondary falls, and need for further rehabilitation. An important part of the treatment during hospital stay is early mobilization, such as getting out of bed and walk within 24 h after surgery. The patients receive physiotherapy exercises each day from Monday to Friday. Additionally, the nurses mobilize the patients on each shift during all week days.

Due to the short hospital LOS, most of the patients are in need of short-term stays in nursing homes for 2–3 weeks, before they are able to return to home. During the short-term stays the patients usually get in contact with a physiotherapist 2–3 times a week. Physiotherapy includes mobilization and gait training [24]. The intervention presented in this protocol contains additional functional training initiated by the nurses and performed at least 4 times a day as part of the daily routine.

### Study design

The study is designed as a single-blind randomized controlled trial (RCT), comparing the effects of additional functional training to usual care alone during short-term stays in nursing homes. This design is the gold standard to test effects of interventions [25, 26].

### Recruitment and study population

Recruitment takes place at Bærum Hospital after hip fracture surgery. Patients with an acute low-energy hip fracture (intracapsular, throchanteric or subtrochanteric) and treated surgically, ≥ 65 years of age, living in their own homes prior to the fracture, and able to give an informed consent, are invited to participate in the study. Patients are excluded if they are unable to walk 10 m with or without a walking aid prior to the fracture, have a score of less than 15 points on Minimal Mental Status Evaluation (MMS-E) in the acute phase, have a pathological fracture, life expectancies of less than 3 months, medical contraindications for training, or are incapable of understanding and speaking Norwegian.

### Randomization and allocation concealment

Four nursing home departments in Bærum municipality that offer short-term stays after hip fracture are included in the study. First, the nursing home departments are matched into two similar groups in terms of anticipated number of patients and culture. Thereafter, the two groups are randomly allocated to either an experimental group that contains a functional exercise program in addition to usual care or to usual care alone (control). At discharge from hospital, the participants are consecutively allocated to the nursing home with the first vacancy. The participants are not in a position to have any influence on the allocation.

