### The interventions

#### The functional training group (experimental group)

The patients who are allocated to the experimental group are receiving a functional training program initiated by the nurses in addition to the usual physiotherapy. The present functional training program is based on transfer activities of daily life, tailored to meet each individual’s needs. It is targeted to the level of difficulty relevant for each participant. The functional training program is performed approximately 4 times a day, 7 days a week during the short-term stay of 2–3 weeks. The nurses will be educated, motivated, guided, and frequently supervised by the research physiotherapists.

The functional training program is inspired by prior research on the effect of a walking skill training program based on ambulatory activities and transfers in patients with total knee [27] and total hip [28] arthroplasty. These patients changed statistically significantly more in walking capacity measured by the 6-min’ walk test, compared to controls. The program is also inspired by the gait and balance program developed by Thingstad et al [29] and performed in patients 4 months after the hip fracture.

The content of the present functional training program is as follows:
*Stepping.* Standing with support, weight transfer without stepping. Progression: Short steps forward and sideways, less support, several repetitions in series of 3.
*Walking in the corridor with a walking aid.* Walk several short distances. Rest on a chair if necessary. Progression: Walk with longer steps, good stride, higher speed, start, stop, and turns. Walk in the corridor as long as you are able to.
*Step-up.* Tapping on to the step but not stepping up. With support: stepping up one or several steps. Progression: Climb up and down the staircase.
*Chair rise.* Raising/lowering on heightened chair with arm support. Progression: Raising/lowering on normal chair with less or without arm support, several repetitions in series of 3.
*Squats.* Stand with arm support. Bend your knees by lowering the body. Progression: Less arm support, deeper bends, several repetitions in series of 3.
*Heel lift.* Stand with arm support. Several repetitions in series of 3.

When transferred to home, the patients are encouraged to continue their exercises at minimum twice daily. They are given a written exercise program with progression before discharge from the nursing homes.

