### Data analysis and statistical power

The sample size is calculated from a small meaningful change in SPPB, the primary outcome measure [43]. A small meaningful change in the SPPB is mean (SD) 0.5 (1.48) points [44]. With a significance level of 0.05 and power of 80% this estimate requires 140 patients, 70 patients in each group. To compensate for potential drop-outs at least 160 patients will be included in the study. All data will be stored at the research server at the hospital. Between-group differences in normal distributed continuous variables will be analyzed with *t*-tests and/or analysis of covariance (ANCOVA) according to the principle of intention-to-treat (ITT). Missing data will be imputed by carrying the last value forward. Effect sizes will be calculated. To examine relationships correlation and/or multiple regression analyses will be used [45]. The significant level is set to *p* < 0.05.

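### Departments, not patients, are randomised, yet the trial is sized and analysed as if patients were independent; if outcomes correlate within departments, the nominal 5% test is anti-conservative

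*Protocol article*

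**What the plan says.** Under Randomization and allocation concealment, the protocol article states: "Four nursing home departments in Bærum municipality that offer short-term stays after hip fracture are included in the study". It continues: "First, the nursing home departments are matched into two similar groups in terms of anticipated number of patients and culture". Next, "the two groups are randomly allocated to either an experimental group that contains a functional exercise program in addition to usual care"; the other group is the control. Patients themselves are not randomised: "At discharge from hospital, the participants are consecutively allocated to the nursing home with the first vacancy".

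The section on the experimental group describes a "functional training program initiated by the nurses in addition to the usual physiotherapy", so the staff of the department deliver the treatment under test.

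Study design calls the trial a single-blind randomised controlled trial and does not mention clusters. Data analysis and statistical power gives the sizing inputs, "A small meaningful change in the SPPB is mean (SD) 0.5 (1.48) points", and the result: "With a significance level of 0.05 and power of 80% this estimate requires 140 patients, 70 patients in each group". At least 160 are to be recruited to cover drop-out. On the analysis it says: "Between-group differences in normal distributed continuous variables will be analyzed with" t-tests and/or ANCOVA by intention to treat. The article names no ICC, design effect or department term.

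**The concern.** The unit that is randomised and the unit that is analysed differ. Patients in one department share nursing staff and routines. The authors matched departments on culture, so they evidently expected culture to differ. Their Discussion also names nurses' adherence under a heavy workload as a challenge. These are ordinary routes to correlated outcomes within a department, and the second SPPB assessment is made after 14 days in that setting.

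If such correlation exists, a patient-level standard error leaves out the between-department variance. Confidence intervals are then too narrow and p-values too small. There is also a limit that does not depend on the ICC. With one randomised group of departments per arm, arm and department group are confounded. The draw has two possible outcomes, so, if they are equally likely, a test based on the randomisation alone cannot give a p-value below 1/2.

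**Working it through.** **Inputs from the article.** Difference 0.5 points, SD 1.48, alpha 0.05, power 80%, 70 per group (140 in total), at least 160 recruited, four departments.

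**Assumptions.** Two-sided test; 1.48 taken as the outcome SD; two equal-sized departments per arm (likely, but not written); ICC from 0 to 0.05. Patients per department, m, is 140/4 = 35 or 160/4 = 40.

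**1. The stated sample size.** The two-sample formula gives n per group = 2 × (1.96 + 0.84)² × 1.48² / 0.5² ≈ 137.5, so 138. The stated 70 does not reproduce. A one-sample or paired formula, without the factor 2, gives 68.8, so 69, which is close to 70 per group. Alternatively, 138 per group may have been read as a total. Neither route contains a design effect. Under independence, power is 51.5% at 70 per group and 57.0% at 80 per group.

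**2. Effect of clustering.** Design effect DE = 1 + (m − 1) × ICC. Effective N = 4m / DE. True two-sided error of the nominal 5% test = 2 × [1 − Φ(1.96 / √DE)]. The error was also simulated with four departments and 20,000 runs per row. The last column is the power of a t-test on department means (2 df, critical value 4.303) for 0.5 points.

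| ICC (assumed) | m | DE | Effective N | True error: formula (simulated) | Power, 2 df |
|---|---|---|---|---|---|
| 0 | 35 | 1.00 | 140 | 5.0% (5.0%) | 22% |
| 0 | 40 | 1.00 | 160 | 5.0% (5.0%) | 24% |
| 0.01 | 35 | 1.34 | 104 | 9.0% (9.5%) | 18% |
| 0.01 | 40 | 1.39 | 115 | 9.6% (9.4%) | 19% |
| 0.02 | 35 | 1.68 | 83 | 13.1% (12.8%) | 15% |
| 0.02 | 40 | 1.78 | 90 | 14.2% (14.7%) | 16% |
| 0.05 | 35 | 2.70 | 52 | 23.3% (23.8%) | 12% |
| 0.05 | 40 | 2.95 | 54 | 25.4% (25.7%) | 12% |

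In the same simulations the 2-df test on department means stayed at about 5% throughout.

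**3. Interval width at ICC 0.02.** SE = 1.48 × √(DE / m).
- m = 40: SE = 1.48 × √(1.78/40) = 0.312; half-width 4.303 × 0.312 = 1.34. Patient-level analysis: 1.96 × 1.48 × √(1/40) = 0.46.
- m = 35: SE = 1.48 × √(1.68/35) = 0.324; half-width 4.303 × 0.324 = 1.40. Patient-level analysis: 1.96 × 1.48 × √(1/35) = 0.49.

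**4. Can more patients make up for it?** With two departments per arm and 138 per arm needed under independence, 80% power requires 2m = 138 × [1 + (m − 1) × ICC]. This has no solution once ICC reaches 2/138 = 0.0145, even before the 2-df penalty.

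**The case against.** **The inflation is conditional.** A reader might infer that the standard errors are certainly too small and that the 5% level certainly fails. The article does not support that. It gives no ICC; at ICC 0 the error is 5%, and with m = 40 it is only about 5.4% at ICC 0.001 and 7.4% at 0.005. Department influence may also be weaker at 3 and 12 months than at the end of a stay of 2–3 weeks. This stands, and the finding is worded accordingly.

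**Case mix is partly protected.** A reader might infer that any case-mix difference between departments is inseparable from treatment. That goes too far. Recruitment is central, SPPB is measured before discharge, patients cannot influence placement, and ANCOVA is among the planned methods. Measured imbalance can therefore be seen and adjusted for, and first-vacancy placement may keep the ICC low. But such placement is not randomisation, and it does not remove unmeasured case mix or effects of staffing and routine that arise after placement.

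**Some details are inferred.** Two departments per arm is presumed. The article does not say how physiotherapists are assigned, so the argument rests on nursing staff and culture, not on shared physiotherapy.

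**An analysis plan may add a department term.** It may. It cannot change a sample size without a design effect, or add departments that were never allocated.

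**Not all the lost power is due to clustering.** Correct. Even under independence the stated inputs give 57% power at 160 patients, not 80%. At ICC 0 the further fall to 24% comes wholly from testing on 2 df.

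**Conclusion.** The mismatch between allocation and analysis is in the text and needs correcting. Its size depends on an ICC that the article does not give. Over assumed ICCs of 0.01, 0.02 and 0.05, with 35 to 40 patients in each of four equal departments, the nominal 5% test has a true error of about 9–10%, 13–14% and 23–26%. The planned inference is sound only if the ICC is essentially zero.

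A reader might also infer that a random department effect would cure the problem. It would not. The department variance rests on 2 df and, with m = 40, was estimated at zero in about 42–51% of simulated trials at ICC 0.01–0.02. If the software then reverts to patient-level degrees of freedom, the error is about 6–7% at ICC 0.02–0.05. No model changes the fact that one group of departments was randomised to each arm.

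**What to change.** In this order:

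1. Describe the trial as cluster-allocated, with one randomised group of departments per arm. State that randomisation alone cannot support a claim at p < 0.05, and that no analysis fully separates department from treatment.
2. Replace the stated 80% power with figures that include a design effect over an assumed ICC range such as 0.01–0.05. Correct separately the 70 per group, which is about half of the 138 that the article's own inputs require under independence.
3. Make the primary SPPB analysis account for department and adjust for baseline SPPB, with inference on between-department degrees of freedom. This can be a 2-df comparison of baseline-adjusted department means. It can also be a random department effect whose degrees of freedom do not revert to patient level when the variance is estimated at zero.
4. Report the ICC, the department means and the difference between departments within each arm. Label any patient-level analysis as assuming no department effect.

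No new data should be needed, since each patient's department is known from placement. The cost is in precision: at ICC 0.02 the half-width grows from 0.46–0.49 to about 1.3–1.4 points, and power for 0.5 points falls to about 12–24% over ICC 0–0.05. Only more departments or patient-level randomisation would remove the underlying limit.

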### Ethics and approvals

Before discharge from hospital, an informed consent will be obtained if the physiotherapist who is recruiting is reassured that the patient fully understands what it implies to participate. The patients with increased risk of falls, restrictions in movement or weight-bearing during training and activity will be focused upon to avoid injuries. The nursing staff will be trained to secure the patients properly to avoid falls and dislocations. All patients recruited to the project will also be offered usual care rehabilitation. The study is funded from Vestre Viken Hospital Trust and is approved by the Regional Committee for Ethics in Medical Research (South-East Norway) (2015/2147). ClinicalTrial.cov NCT02780076.

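### One random draw assigns two groups of departments; patients then reach an arm by first vacancy, so the patient-level randomisation and concealment the article claims are not provided

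*Protocol article*

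**What the plan says.** All references are to the protocol article.

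- **Study design:** "The study is designed as a single-blind randomized controlled trial (RCT".
- **Abstract, Methods/design:** "Inclusion and randomization will take place during hospital stay".
- **Randomization and allocation concealment, department level:** four departments take part, and before any draw they are paired off into two sets thought alike in expected caseload and culture. The one random step is then described: "Thereafter, the two groups are randomly allocated to either an experimental group"; the other set gives usual care alone.
- **Same section, patient level:** "At discharge from hospital, the participants are consecutively allocated to the nursing home with the first vacancy".
- **Same section, the only safeguard given against steering of placement:** "The participants are not in a position to have any influence on the allocation".
- **Ethics and approvals, on entry to the trial:** "an informed consent will be obtained if the physiotherapist who is recruiting is reassured that the patient fully understands".
- **Data analysis and statistical power:** 70 patients per group, compared by t-tests and/or ANCOVA. The unit is the patient, and no covariates are named.

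**The concern.** The abstract and the section heading lead a reader to expect that chance decides each patient's arm and that nobody involved in enrolment can foresee it. The stated rule gives neither assurance. Bed availability on the day decides the arm, in departments whose arm was set beforehand.

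A patient-level t-test takes its justification from chance assignment of patients. If the type of patient enrolled, or the day of discharge, is related to which department has a bed, the groups can differ in prognosis before the intervention starts. The primary SPPB comparison then mixes that difference with the training effect. The single draw between groups of departments does not protect against this. It also cannot separate the training from whatever else differs between the two groups of departments.

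**Working it through.** **1. Count the random acts.** The plan gives no figure for allocation, so the check is to set its statements side by side.

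| Step | Unit | Decided by chance? |
|---|---|---|
| Matching | four departments into two groups (presumably two each; the split is not given) | no |
| Assignment of groups to arms | two groups | yes, once |
| Placement of a patient | each participant | no, by first vacancy |

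The total is one random assignment of groups and none of patients. A draw between departments is not something that happens during a patient's hospital stay. The abstract's sentence therefore describes a step that the allocation section does not contain.

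**2. Who could foresee the arm?** Once the draw is made, the department determines the arm, so knowing the next vacancy means knowing the arm. The stated safeguard covers participants only. Concealment also has to cover those who enrol and place patients, and entry depends partly on judgement:
- the recruiting physiotherapist judges whether the patient understands what participation implies (Ethics and approvals);
- medical contraindications for training exclude a patient (Recruitment and study population);
- patients going directly home are excluded (Discussion).

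Project physiotherapists train and supervise nurses in the experimental departments (The interventions; Adherence to the program), so some project staff must know which departments those are. The article does not say whether anyone who recruits sees the vacancies.

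**3. What a given amount of selection would do.** Inputs from Data analysis and statistical power: SD 1.48, 70 per group, significance level 0.05. The test is taken as two-sided, which the article does not state. The shift *b*, the mean SPPB difference due to selection alone, is an assumption; the documents give no value.

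Standard error of the difference: 1.48 × √(2/70) = 0.250.

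False-positive rate with no true effect: Φ(−1.96 + *b*/SE) + Φ(−1.96 − *b*/SE).

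| Assumed *b* (points) | *b*/SE | False-positive rate |
|---|---|---|
| 0 | 0 | 5% |
| 0.1 | 0.40 | 0.068 (about 7%) |
| 0.2 | 0.80 | 0.126 (about 13%) |
| 0.3 | 1.20 | 0.224 (about 22%) |

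Every shift shown is smaller than the 0.5 points for which the trial is sized. The figures are for an unadjusted comparison. They treat patients as independent, so they do not include any department effect. The 70 per group is used here as stated; whether it follows from its own inputs is a separate matter.

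**The case against.** **There is a random step, and a cluster-randomised trial is still an RCT.** This is correct. The Study design section never says that patients are individually randomised, and it would be wrong to read the trial as having no randomisation at all. But the abstract places randomisation in the hospital stay, and the sample size and analysis treat the patient as the randomised unit. The description needs correcting, and the correction must keep the department-level draw.

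**Bias is inferred, not shown.** This also stands. A reader might infer that staff steer patients, or that selection bias is certain. The article says neither who manages vacancies nor who sees them. A fuller protocol might describe how information is withheld from recruiters, but it could not turn a first-vacancy rule into chance assignment of patients.

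**Faster turnover in the training arm.** A reader might suspect that training shortens stays, so that experimental departments fill and empty faster. The article gives 2–3 weeks for the stay and reports no effect on it. Faster turnover would bias the comparison only if prognosis also varied with discharge timing. It should not be claimed.

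**Group sizes are not wholly uncontrolled.** Departments are matched on the number of patients expected. That is imperfect control, but it is some.

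**ANCOVA is allowed, and baseline comes first.** Consent and baseline assessment precede discharge, and assessors are described as blinded, so distorted baseline scores are less likely than selective enrolment or discharge timing. Adjustment for baseline SPPB would reduce the selection that acts through that score. The rates above would then apply only to what remains through unmeasured prognosis. However, the article leaves the choice between t-test and ANCOVA open and does not say that baseline SPPB is a covariate.

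**Conclusion.** The point holds in a limited form. The article states outright an allocation rule that does not deliver what its abstract and section heading claim: chance enters once, between two groups of departments, and each patient's arm follows from bed availability. This is a conflict within the document, not detail left out of a condensed article.

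The stated rule makes selective enrolment or discharge timing possible, but the documents do not show that either occurs. The false-positive rates of about 7%, 13% and 22% illustrate assumed shifts of 0.1, 0.2 and 0.3 points under an unadjusted two-sided test; they do not estimate bias in this trial. The finding about the allocation rule does not depend on them. Because the rule decides how far the primary comparison can be read as causal, and cannot be repaired once patients are placed, it should be dealt with as early as possible.

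**What to change.** 1. Complete eligibility, consent and baseline SPPB before anyone seeks bed information. Consent and baseline already precede discharge, so the new element is withholding vacancy information until they are done.
2. When both arms have a bed, take the arm from a concealed, computer-generated list held off the ward. When only one arm has a bed, place by vacancy and flag the patient.
3. Log the vacancies in all four departments at each placement.
4. Fix the primary analysis as adjusted for baseline SPPB. Report the list-allocated patients as a sensitivity analysis, and state that this subset may be small, since the documents do not say how often both arms have a bed.
5. State that department effects remain confounded with arm, which the list cannot remove.

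If a list is not feasible, correct the abstract, the Study design section and the allocation section to read: *two matched groups of departments randomly allocated to arm, with non-random, vacancy-based placement of patients*. Limit the conclusions accordingly. For patients already placed by vacancy, only the corrected description and the baseline adjustment can help.

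Cost: a short amendment, someone off the ward to hold the list, a vacancy log, and a less favourable design label.
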